### Statistical analysis

All analyses will use an intention-to-treat approach. Baseline patient demographics, severity of illness, ICU length of stay, mortality, and nutritional markers will be tabulated according to the treatment group. Initial exploratory data analysis will involve calculation of summary statistics and comparison between treatment groups using non-parametric (Wilcoxon), parametric (*t* test), and Fisher’s exact tests as appropriate, as well as construction of trajectory plots according to the treatment group. The co-primary outcomes of average daily energy and protein delivery will be compared between treatment and control groups with two-sample unpaired *t* tests, with statistical significance for each set conservatively at two-sided values of 0.025 to limit the family-wise type 1 error for the two co-primary outcomes to less than 0.05 overall.

All secondary outcomes will be regarded as exploratory and hypothesis-generating, with no multiple comparison adjustment to conventional 5% type 1 error thresholds. Group differences for change from baseline at selected time points in continuous outcome variables, including QMLT, will be compared after adjustment for initial values using analysis of covariance (ANCOVA) regression models, initially unadjusted, and subsequently adjusted as described below for other regression models. Natural logarithmic transformations may be applied to stabilise variance within these or other linear models if appropriate. The relationships between calorie deficits using both prescribed calories (25 kcal/kg) and MEE and protein adequacy and the outcome measures (QMLT change, muscle strength, diagnosis of ICUAW, and physical function at ICU discharge) will be explored using linear or logistic regression analyses, with adjustment for likely confounders and any baseline variable found to show substantial imbalance between treatment groups. Finally, a population-averaged generalised linear model using a generalised estimating equation (GEE) approach with an unstructured working correlation matrix and robust standard error estimates adjusted for clustering within individual subjects will be applied to these longitudinal data to evaluate the overall associations of the vector of (untransformed or log transformed) outcome variables with treatment group across multiple time points. Multiple imputations for missing data may be used to support conclusions from other generalised linear models constructed without imputation of missing data. Data analysis will be carried out using the Statistical Package for the Social Sciences (SPSS) (IBM® SPSS® Statistics Premium Grad Pack Version 22.0) or Stata Corporation (Stata Statistical Software: Release 15. College Station, TX: StataCorp LP; 2017).

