### Standard care group

The comparator group will receive standard nutrition care [39], which includes commencing a standard commercially available 1.0 kcal/ml enteral formula (Nutrison® 1.0 kcal, Nutricia, Wuxi, China), providing 40 g protein and 1000 kcal per litre. Liquid nutrient will be commenced using our ICU nutrition protocol (Appendix), and the target rate will be set at 25 kcal/kg ideal body weight (IBW) [1]. This strategy is designed to prescribe 1.0 g/kg protein and 25 kcal/kg of energy per day, however it is anticipated participants will receive less than this due to interruptions to nutrition therapy [39]. For participants below or within the IBW range (defined as a BMI between 18.5–25 kg/m^2^ for 18–65 years and 22–27 kg/m^2^ for ≥ 65 years [40]), actual body weight will be used. For participants with BMI ≥ 32 kg/m^2^, an adjusted IBW will be used (IBW + 25% (actual weight – IBW)) [41].

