### Intervention group

The intervention group will receive their nutrition care based on the FEED protocol (Fig. 2, FEED protocol). It is anticipated that this will provide 1.5 g/kg protein and 25 kcal/kg of energy per day. The enteral formula will be a 1.25 kcal/ml formula (Nutrison® Protein plus, Nutricia, Zoetermeer, The Netherlands), providing 1250 kcal and 63 g protein per litre. The target formula volume will be determined based on 25 kcal/kg IBW, and the difference between the protein provided from the enteral formula and the target protein requirement of 1.5 g/kg IBW will be calculated. This difference will be met using protein powder (Beneprotein®, Nestle Health Sciences, Switzerland), provided in 6 g protein boluses (1 scoop of powder (7 g), provides 6 g of protein) over the day. Beneprotein® is a commercially available product that contains 100% whey protein isolate. To ensure that the target volume of formula is delivered, at 16:00 each day, the ICU bedside nurse will calculate the volume of formula provided, compared to the target volume, and then adjust the feed rate to aim to deliver the remaining feed volume over the 8-h period to midnight, with a maximum feeding rate of 150 ml/h [11]. The data on compliance to the feeding protocol will be collected.

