### Primary outcomes

The co-primary outcomes are mean daily protein and energy provided over the 15-day study period. The provision of protein and energy will be calculated on a daily basis and will be determined taking into account all sources; this includes nutrition therapy (enteral formula, protein supplements, and parenteral formula), dextrose, and propofol. The mean protein and energy provided will be determined, by adding the daily provision over the 15-day study period (the 14 complete calendar days). The provision of any nutrition prior to commencing the study protocol will be collected and reported but not included in the primary outcome analysis.

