### Sample size

A sample size of 60 is based on observational data [45], where daily protein intake, mean (SD), was 50.8 g (20.1 g) protein per day; therefore, 29 participants per group will provide 80% power (two-sided *α* 0.05) to detect a minimum difference of a 15-g protein between groups. While there is limited data on change in muscle mass using ultrasound, using the data from the VALIDUM study, mean (SD) QMLT of 1.3 (0.6) cm [22], a sample size of 28 participants in each group will also provide over 80% power to detect a mean difference of 0.5 cm in QMLT.

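### The co-primary t tests on absolute daily protein and energy leave out dosing weight, which sets every patient's target and can be known before randomisation; adjusting for it costs almost nothing, but the gain is uncertain.

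*Protocol article*

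**What the plan says.** Under Primary outcomes, "The co-primary outcomes are mean daily protein and energy provided over the 15-day study period". The Sample size section plans the protein difference in grams per day, not per kg or as a share of target.

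Prescription is by weight in both arms. In the Standard care group section, "the target rate will be set at 25 kcal/kg ideal body weight (IBW"), with actual or adjusted weight substituted in stated BMI ranges. In the Intervention group section, the formula volume is set from 25 kcal/kg IBW and the gap to "the target protein requirement of 1.5 g/kg IBW will be calculated". Baseline data collection lists ulna-based height, bed-scale weight and BMI among measures that reflect the patient's status at or before randomisation. Randomisation and blinding specifies simple 1:1 randomisation.

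The Statistical analysis section then says: "The co-primary outcomes of average daily energy and protein delivery will be compared between treatment and control groups with two-sample unpaired" *t* tests, each at a threshold "set conservatively at two-sided values of 0.025 to limit the family-wise type 1 error for the two co-primary outcomes". ANCOVA appears only for change-from-baseline secondary outcomes. Those models are run first without and then with further covariates, which are likely confounders and "any baseline variable found to show substantial imbalance between treatment groups".

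**The concern.** A patient's target in grams and kilocalories is a fixed multiple of dosing weight, so heavier patients should on average receive more in either arm. Part of the spread in the outcome is therefore predictable from a number available before allocation. An unadjusted comparison treats that part as noise. With simple randomisation of 60 patients, a chance difference in mean weight also passes straight into the estimated difference in protein and energy.

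What is at stake is precision. The protocol names the primary test outright, so this choice is not left to an unseen analysis plan.

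**Working it through.** **Inputs from the protocol (Sample size, Statistical analysis).** Daily protein mean 50.8 g, SD 20.1 g; target difference 15 g; 29 per group (60 recruited, so about 30 per arm); alpha 0.05 in the sample size and 0.025 per co-primary in the test.

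**Inputs not in the documents (assumptions).** Mean dosing weight 70 kg; dosing-weight SD 5 to 15 kg; delivery proportional to weight, with delivered g/kg independent of weight. Alternatively, a correlation ρ between dosing weight and delivered protein of 0.2 to 0.6.

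**1. The plan's own figure.** n per group = 2 × (20.1/15)² × (1.960 + 0.842)² = 28.2, rounded up to 29. This reproduces the stated size. With the noncentral *t*, 29 per group gives 79.7% power at alpha 0.05.

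**2. The same test at the alpha that will be used.** At 0.025, unadjusted power is 70.4% with 29 per group and 72.1% with 30. Weight plays no part in this drop.

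**3. Variance explained by dosing weight.** Slope = 50.8/70 = 0.726 g per kg. R² = (0.726 × SD of weight)² / 20.1². Residual SD = 20.1 × √(1 − R²). Power is from the noncentral *t* with one further degree of freedom lost, 29 per group, alpha 0.025:

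| Dosing-weight SD (kg) | R² | Residual SD (g) | Power |
|---|---|---|---|
| not adjusted | – | 20.1 | 70.4% |
| 5 | 3% | 19.8 | 72% |
| 8 | 8% | 19.2 | 74% |
| 10 | 13% | 18.7 | 77% |
| 12 | 19% | 18.1 | 80% |
| 15 | 29% | 16.9 | 86% |

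**4. The same gain by correlation.** Residual SD = 20.1 × √(1 − ρ²). With 30 per arm at alpha 0.025, power goes from 72.1% unadjusted to 74.0% (ρ = 0.2), 76.5% (0.3), 80.0% (0.4), 84.7% (0.5) or 90.2% (0.6). At ρ = 0.2 the gain is about 2 points.

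**5. Chance imbalance.** With 30 per arm and an assumed weight SD of 10 kg, the difference in mean weight has standard error 10 × √(2/30) = 2.58 kg. In protein this is 0.726 × 2.58 = 1.9 g, and 1.96 × 1.87 = 3.7 g at the 95% limit, about a quarter of the 15 g target difference. Adjustment removes this component.

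**6. Energy.** The protocol gives no planning SD and no effect size for energy delivery, so steps 3 to 5 cannot be repeated.

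**The case against.** The strongest reply is that nothing here is an error. A two-sample *t* test on randomised arms is valid and unbiased. It matches the planned unadjusted difference in grams, and the 20.1 g SD, being a spread across patients, presumably already includes their variation in weight. That stands: the loss is efficiency forgone, not a shortfall against the plan's own 80% at alpha 0.05.

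Second, the gain may be small. The Background and the Standard care group section stress interruptions and feeding intolerance, which are not functions of weight. Dosing weight is also compressed by design: it is based on IBW, and only 25% of excess weight is added back at BMI ≥ 32. That makes the 12 to 15 kg rows less likely. This also stands, and is why the range starts at 5 kg.

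Third, weight is not wholly ignored, because protein adequacy and calorie deficit are secondary outcomes set against requirements or 25 kcal/kg. That is true, but neither enters the primary comparison.

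A reader might also infer that adjustment would restore the stated power. The documents do not support this. The fall from 79.7% to 70.4% comes entirely from the change of alpha between two sections. Under the assumptions above, adjustment makes up more than half of that gap only from a dosing-weight SD of about 10 kg; at 8 kg it makes up 4.1 of 9.3 points.

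**Conclusion.** The point holds as a low-cost improvement in efficiency. The plan fixes an unadjusted test of absolute amounts although a baseline variable that determines every target is available. The direction of the gain is secure wherever delivery tracks weight at all. Its size is not: for protein with 29 per group at alpha 0.025, power moves from 70% to between 72% and 86% across assumed dosing-weight SDs of 5 to 15 kg, on a 70 kg mean and proportional delivery. With 30 per arm and a correlation of 0.2, it is about 2 points. For energy the argument is qualitative only.

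It should not be read as saying that the primary analysis is biased or invalid. The alpha mismatch is a separate issue and needs its own correction.

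The imbalance-driven covariate rule is a lesser point. It is written for the exploratory regressions, where adjusting for likely confounders is reasonable, but the between-arm ANCOVA models inherit it. Observed imbalance does not show that a variable is prognostic, and the rule carries no threshold. All of these outcomes are declared exploratory, so little depends on it.

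**What to change.** In the Statistical analysis section, make the primary analysis of each co-primary outcome a prespecified linear regression (ANCOVA) on treatment arm and the dosing weight used for the prescription. Keep the unpaired *t* test as a supportive analysis. Define the covariate from pre-randomisation height and weight by one rule applied to every patient, so that it cannot depend on allocation.

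For the exploratory between-arm ANCOVA models, replace selection by observed imbalance with a short list fixed in advance for prognostic value: the baseline value of the outcome plus one or two variables already collected, such as age and APACHE II.

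The cost is a change of wording and one degree of freedom in each primary model. No new data and no change to recruitment are needed.

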## Abstract

**Background:**

Current guidelines for the provision of protein for critically ill patients are based on incomplete evidence, due to limited data from randomised controlled trials. The present pilot randomised controlled trial is part of a program of work to expand knowledge about the clinical effects of protein delivery to critically ill patients. The primary aim of this pilot study is to determine whether an enteral feeding protocol using a volume target, with additional protein supplementation, delivers a greater amount of protein and energy to mechanically ventilated critically ill patients than a standard nutrition protocol. The secondary aims are to evaluate the potential effects of this feeding strategy on muscle mass and other patient-centred outcomes.

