## Study objectives

### Co-primary

The primary aim of this pilot study is to determine whether a volume-based feeding protocol with supplemental protein potentially improves the average daily protein and energy delivery, when compared to standard care in mechanically ventilated critically ill patients.

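### The fixed 0.025/0.025 split for the two co-primary outcomes is valid but costs power, mainly on energy; Holm's step-down keeps the same family-wise limit

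*Protocol article*

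**What the plan says.** All places are in the protocol article.

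- **Primary outcomes:** "The co-primary outcomes are mean daily protein and energy provided over the 15-day study period".
- **Statistical analysis:** each outcome gets its own unpaired t test between the arms. The threshold is fixed in these words: "with statistical significance for each set conservatively at two-sided values of 0.025 to limit the family-wise type 1 error". The stated ceiling for the pair is 0.05. The section gives no step-down, testing order or passing-on of unused alpha.
- **Study objectives, Co-primary:** the aim is to see whether the intervention "potentially improves the average daily protein and energy delivery". The abstract's Background puts it as whether the protocol "delivers a greater amount of protein and energy to mechanically ventilated critically ill patients than a standard nutrition protocol". Neither place says whether one significant outcome is enough or both are needed.
- **Standard care group** and **Intervention group:** the arms are designed around 1.0 and 1.5 g/kg protein per day respectively, and both around 25 kcal/kg energy per day.
- **Sample size:** based on protein alone, where the source data "mean (SD), was 50.8 g (20.1 g) protein per day" and the target difference is 15 g. No effect, SD or power is given for energy.

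**The concern.** With a fixed split, the 0.025 assigned to one outcome stays locked there even after that outcome has been shown. Suppose protein gives p = 0.001 and energy gives p = 0.03. Under the rule as written, energy is not significant. Under Holm it is, and the family-wise error is still at most 0.05.

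The loss is unlikely to fall evenly. The protein prescriptions differ by half a gram per kilogram, whereas the energy targets are equal. Energy should therefore differ mainly through fuller delivery of the same target, and the article's Background and Discussion warn that intolerance could reduce delivery. Protein is the likelier first rejection, and energy is the outcome that would benefit from the released alpha. At stake is some power on one of two co-primary outcomes in a trial of 60.

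**Working it through.** **1. The plan's own figures.**
- Family-wise error of the split: at most 0.025 + 0.025 = 0.05 whatever the correlation. If the outcomes are independent it is 1 − 0.975² = 0.0494. The article's claim of error control is right.
- Sample size: n per group = 2 × (1.960 + 0.842)² × 20.1² / 15² = 2 × 7.85 × 404.01 / 225 = 28.2, rounded up to 29. This reproduces the article's figure at two-sided 0.05. The standardised protein effect is 15 / 20.1 = 0.746 SD.

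**2. Holm has the same family-wise limit.** Holm compares the smaller p with 0.025 and, only if that is significant, the other p with 0.05.
- Both null hypotheses true: a false claim requires the smaller p to be ≤ 0.025, exactly as under the split, so the error is identical and at most 0.05.
- One null hypothesis true: a false claim requires that outcome's p to be ≤ 0.05, so the error is at most 0.05.

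No assumption about correlation is used.

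**3. Holm never rejects less.** Any p ≤ 0.025 is rejected under both rules. For energy, the extra rejections are exactly the trials with protein p ≤ 0.025 and energy p above 0.025 but no more than 0.05.

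**4. Size of the loss.** Simulation of 100,000 trials per scenario: 30 per arm, bivariate normal outcomes, two-sample t tests, protein effect 0.746 SD. The energy effect and the correlation r are assumptions.

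| Energy effect (SD) | r | Energy power, fixed split | Energy power, Holm | Gain (points) |
|---|---|---|---|---|
| 0.4 | 0.5 | 0.234 | 0.316 | 8.2 |
| 0.4 | 0.9 | 0.233 | 0.330 | 9.7 |
| 0.5 | 0.5 | 0.364 | 0.454 | 9.0 |
| 0.5 | 0.8 | 0.364 | 0.465 | 10.1 |
| 0.5 | 0.9 | 0.365 | 0.474 | 10.9 |
| 0.6 | 0.5 | 0.511 | 0.593 | 8.2 |
| 0.6 | 0.8 | 0.512 | 0.601 | 8.9 |
| 0.746 | 0.5 | 0.723 | 0.777 | 5.4 |
| 0.746 | 0.8 | 0.719 | 0.766 | 4.7 |
| 0.746 | 0.9 | 0.723 | 0.762 | 3.9 |

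**5. Error rates in the same simulation.** With no effect on either outcome, the chance of any false claim is the same for both rules: 0.047 at r = 0.5, 0.039 at r = 0.8 and 0.035 at r = 0.9. With a protein effect of 2 SD and no energy effect, Holm's false-positive rate for energy is 0.051 at r = 0.5 and 0.049 at r = 0.8, which is 0.05 within simulation error. The fixed split gives 0.025. Holm thus uses the error allowance the article sets, where the split leaves half of it unused.

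**The case against.** The strongest defence is that nothing here is wrong. The split is valid, prespecified and described by the article itself as conservative, and in a pilot a plain rule has merit. It also has simple matching 97.5% confidence intervals. Under Holm, an energy result with p = 0.03 would be significant while its 97.5% interval included zero. For a trial meant to supply estimates for a larger one, that is a genuine advantage of the split, and it stands.

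A second defence concerns timing. Screening began in August 2015, and bedside nurses calculate delivered volume every day, so delivery is visible to unblinded staff. Relaxing a threshold after the start invites suspicion. That bears on when and how the change is made; it does not show that the fixed split performs as well.

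Three stronger readings are tempting but unsupported:

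- *The aim succeeds only if both outcomes are significant, so no split was needed.* A reader might infer this from the pairing of protein and energy in the aim. No section states such a rule. Setting significance for each outcome while controlling the family-wise error reads more naturally as two separate claims, and the objective's wording is tentative: "potentially improves the average daily protein and energy delivery, when compared to standard care".
- *The split is a statistical error.* Its error control is confirmed above.
- *An energy p of 0.03 would stop the programme, or would mean that energy delivery was not improved.* The article ties no progression decision to that p value. Missing 0.025 means only that the result is not significant at that level.

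**Conclusion.** The point holds as a matter of efficiency. For two separate claims under a family-wise limit of 0.05, the fixed split is uniformly less powerful than Holm, and that conclusion needs no numerical assumption.

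The size does need assumptions. The loss on energy is about 4 to 11 percentage points of power with 30 per arm, normally distributed outcomes, a protein effect of 15/20.1 SD, energy effects of 0.4 to 0.75 SD and correlations of 0.5 to 0.9. Only the protein figures and the trial size come from the article. That protein is the likelier first rejection is inferred from the prescriptions and is not stated. The improvement is cheap and worth making; leaving the split in place would not invalidate the trial's conclusions.

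**What to change.** In the Statistical analysis section, keep the t tests and replace the fixed split with: *The smaller of the two co-primary p values is compared with two-sided 0.025; if it is significant, the other is compared with two-sided 0.05. The family-wise type I error is at most 0.05, and a separate claim is made for each outcome.* Do not add a rule that both must be significant. The article has not chosen one, and if it were wanted, testing each outcome at 0.05 would already suffice.

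Make the change before unblinding, and record it as a dated amendment with its reason, so that it cannot be read as a response to results.

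The cost is one sentence and an amendment, with no extra patients or data. Confidence intervals that match Holm are less simple, so report 97.5% intervals, or 95% intervals labelled as unadjusted, alongside the tests, and note that a 97.5% interval may include zero when the second test is significant.

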### Randomisation and blinding

We will use a simple randomisation system to assign participants [1:1] to receive either standard care or the intervention. Allocation will be concealed using sequentially numbered opaque sealed envelopes, held by research personal not involved with the study. If the participant or the person responsible wishes to withdraw consent at any time, all study procedures will cease and the participant will receive standard ICU care as directed by the clinical team. Due to the nature of the intervention, the study is single-blinded. However, outcomes of muscle strength and physical function will be measured by an investigator blinded to the group allocation. Data analysis will be performed using a binary treatment code to maintain group allocation of blinding until the results are finalised.

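### Adding covariates because the arms look imbalanced is a poor rule for the adjusted secondary analyses; a prognostic set fixed in advance does better

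*Protocol article*

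**What the plan says.** All references are to the protocol article.

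- **Arm comparisons of change from baseline** (Statistical analysis). Continuous outcomes, QMLT among them, "will be compared after adjustment for initial values using analysis of covariance (ANCOVA) regression models". These models are "initially unadjusted, and subsequently adjusted as described below for other regression models".
- **The rule referred to** is in the sentence on the nutrition-outcome regressions, which adjust for likely confounders and also for "any baseline variable found to show substantial imbalance between treatment groups". It has two parts: likely confounders, and variables that turn out imbalanced. The article gives no threshold for imbalance.
- **Exposures in those regressions.** The sentence begins "The relationships between calorie deficits using both prescribed calories (25 kcal/kg) and MEE and protein adequacy and the outcome measures". The explanatory variable is therefore delivered nutrition, not treatment arm.
- **Status.** "All secondary outcomes will be regarded as exploratory and hypothesis-generating". The co-primary protein and energy outcomes "will be compared between treatment and control groups with two-sample unpaired" *t* tests, with no covariates.
- **Allocation** (Randomisation and blinding) is simple 1:1 randomisation. Baseline data collection and the Fig. 3 legend list well over ten baseline variables, including age, BMI, APACHE II, SOFA, Charlson index and Katz index.

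**The concern.** In a randomised comparison, a covariate helps because it predicts the outcome. A chance difference between arms says nothing about that. A rule that lets variables in on imbalance has three effects on the arm comparisons:

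- An irrelevant variable that happens to differ between arms is added. It costs a degree of freedom and, being correlated with arm, widens the standard error.
- A prognostic variable that is balanced, and not on the list of likely confounders, is left out. Its share of the outcome variance stays in the residual.
- The covariate set, and even its size, is known only once baseline data have been compared by arm. Analysing under a coded treatment label hides which arm is which, but it does not remove this dependence.

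The adjusted test then tends to be conservative. When a prognostic variable is imbalanced the estimate is corrected for it. When it is balanced the estimate is already good, but the standard error is still computed as if that variance were noise.

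In the regressions on calorie deficit and protein adequacy, a confounder is a variable related to both delivered nutrition and outcome. Imbalance between arms does not identify such variables.

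At stake is the precision of the adjusted QMLT and similar estimates. The Discussion describes these assessments as essential for planning a larger multicentre study.

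**Working it through.** **1. The plan's own figures.** The plan gives no figure for the covariate rule. Its sample size reproduces:

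- Protein: n = 2 × (1.960 + 0.842)² × 20.1² / 15² = 28.2, so 29 per group. Power at 29 is 81.1% (normal) or 79.7% (t).
- QMLT: 0.5/0.6 = 0.833 SD. With 28 per group, 0.833 × √(28/2) − 1.960 = 1.158, which gives 87.7% (normal) or 86.5% (t). This agrees with the stated power of over 80%.

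**2. How many variables chance alone would select.** Assume 14 independent candidates.

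- Rule of a standardised difference above 0.25, 30 per arm: z = 0.25 × √(30/2) = 0.968, two-sided tail 0.333, so 14 × 0.333 = 4.7 variables. Simulation with simple randomisation gives 4.8, with a 95% range of 1 to 8.
- Rule of p < 0.05: 14 × 0.05 = 0.7 variables.

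The model size is therefore itself random.

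**3. Arm comparisons.** Assumptions not in the documents: baseline value of the outcome always in the model and explaining 25% of variance; 3 prognostic covariates among the 14, jointly explaining 20% or 40%; true effect 0.65 SD; two-sided 5% level; imbalance judged by p < 0.05 or by a difference above 0.25 SD. There were 60 patients under simple randomisation. The comparator is the baseline value plus the 3 prognostic covariates, fixed.

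| Prognostic covariates already adjusted as likely confounders | Loss of power against fixed set | Type I error under the rule |
|---|---|---|
| All 3 | about 1 to 6 points (83–97% against 89–98%) | 5.0–5.7% |
| None | about 10 to 18 points | 2.4–4.5% |

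With 3,000 runs the simulation error near 80% power is √(0.8 × 0.2 / 3000) = 0.7 points, so the 1-point end is close to noise.

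A separate simulation (29 per arm, all candidates prognostic) covers the middle ground. With 2 of 5 covariates always adjusted, power is 84–92% against 90–98%, a loss of about 4 to 9 points, and type I error is 2.9–4.7%. With one weak covariate explaining 10% of variance and not on the list, the effect is small: power 80–82% against 84%, type I error 4.4–4.6%.

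**4. Against the model without extra covariates.** The adjusted model lost power only with 14 candidates, 20% of variance explained and no prognostic covariate on the list: 77–79% against 80–81%. With 2 or 3 of the 3 prognostic covariates on the list, it gained (for example 85–88% against about 80% under the p < 0.05 rule with 20% explained).

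**5. Nutrition-outcome regressions.** Assume one confounder, correlated 0.3 or 0.5 with exposure and with outcome, and no true nutrition effect.

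- The imbalance clause selects this confounder in about 5% of trials (p < 0.05) or 33–34% (difference above 0.25).
- If it is not on the list, the false-positive rate is 9–41% or 8–30% respectively, against 9–43% with no adjustment at all.
- If it is always included, the rate is 5% and there is no bias.

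The clause is thus a weak safety net for a confounder that the list misses, and does nothing for one already on it.

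**The case against.** The strongest reply is that imbalance is only the second of two criteria. Likely confounders come first and enter whatever the imbalance. The outcome's initial value, usually the best predictor, is always in the ANCOVA. The models without the extra covariates are fitted first, and everything affected is labelled exploratory. One may add that adjusting for an imbalanced prognostic variable removes a real distortion in the trial at hand.

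Most of this stands, and it rules out several stronger readings that a reader might infer:

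- *Covariates are chosen by imbalance alone.* The sentence names likely confounders first.
- *The nutrition-outcome regressions use the wrong criterion.* The right one is stated. The high false-positive rates above apply only to confounders left off the list.
- *The adjusted results will be less powerful than the simpler ones.* This happens only in some settings.
- *The list of likely confounders is missing.* It may be in a full protocol or analysis plan that is not shown, so its absence is no error.

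The reply does not rescue the clause itself. A fixed prognostic set corrects a chance imbalance in those variables equally well, and also gains precision when there is none. An analysis plan could set a threshold for imbalance, but it could not name in advance the variables that will enter through it.

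**Conclusion.** The point holds for the added imbalance clause, in the second-step ANCOVA and, to a lesser degree, in the nutrition-outcome regressions. Against a fixed prognostic set, the cost in power runs from about 1 to 6 points (all prognostic variables already listed) to about 10 to 18 points with a conservative test (none listed). Where the trial falls depends on a list that the article does not give.

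The sizes rest on assumed correlations, candidate numbers, thresholds and an effect of 0.65 SD. They shrink when the covariates are weakly prognostic. The direction against a fixed prognostic set was the same in every setting tried.

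The co-primary comparisons and the sample size are untouched. This is a worthwhile improvement to exploratory analyses of a pilot, and no threat to its main conclusion.

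**What to change.** - Delete the imbalance clause.
- For the adjusted ANCOVA, use the outcome's baseline value plus a short prognostic set fixed before unblinding, whatever the observed imbalance. Choose it from data already collected, for example age, APACHE II and BMI.
- For the regressions on calorie deficit and protein adequacy, keep only confounders chosen on subject-matter grounds for their relation to delivered nutrition and outcome.

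The cost is about one sentence in the Statistical analysis section and no new data. If the fixed covariates prove not to be prognostic, about 2 points of power are lost (80.4% to 78.4% in simulation).
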